## Methods

### Study design and ethical aspects

The study is designed as an assessor-blind, randomized controlled trial with an intervention group (MCT-OCD) and a care as usual control group. The study is registered with the German Registry for Clinical Studies (DRKS00013539), was approved by the local ethics committee (Deutsche Gesellschaft für Psychologie; LJ112017), and will be conducted in accordance with the Declaration of Helsinki. All information revealing patient identity (name, e-mail address, etc.) will be stored separately from psychopathological data in a locked cabinet. A coding list will be created in which the names of the patients are linked to the corresponding identifiers. The coding list will only be available in paper form and will be kept in a locked cabinet. Once data collection is completed, the coding list will be destroyed. The anonymized data will be archived for 10 years. Written informed consent will be obtained from all participants. If participants withdraw their consent to participate in the study, the reasons will be carefully documented and the collected data will be destroyed and deleted. Only staff members directly involved in the project and approved by the principle investigator will have access to the final dataset.

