### Sample size

To detect a medium to large effect size of *d* = 0.80, with an alpha level of α = 0.05 and a power of 0.80, G*Power [66] calculated a sample size of *N* = 70. As a dropout rate of 15% is expected, a sample of *N* = 80 patients with OCD will be recruited and randomized to the two groups (*n* = 40 MCT-OCD, *n* = 40 usual care control group). A diagnosis of OCD will be verified by the Mini International Neuropsychiatric Interview 5th Ed. (MINI 7.0.2) [67], which serves to elucidate further psychiatric diagnoses based on the *Diagnostic and Statistical Manual of Mental Disorders* (5th ed.) (*DSM-5*).

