### Randomization and assessor blindness

The randomization will be carried out via a computerized randomization plan, which will not be accessible to the assessors (blinded). Randomization will take place after baseline assessment (−t1): Patients will receive a prepared, sequentially numbered envelope with a letter stating the group they are allocated to (intervention group [MCT-OCD] or care as ususal control group) from the person coordinating the study. After the last MCT-OCD session (or 8 weeks after –t1 for the usual care control group), patients will be invited to participate in the post assessment (t1) in order to re-assess primary and secondary outcomes. Three months later, participants will receive a link to an online survey for the follow-up assessment (t2) via email. Subsequently, participants who were assigned to the care as ususal control group will be allowed to participate in the MCT-OCD to improve adherence. Withdrawal from the intervention or assessments will be possible at any time. Before the post assessment, patients will be reminded not to reveal their intervention condition to the assessor.

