### Statistical analyses

An intention-to-treat analysis (considering patients who provide baseline data) as well as complete cases analysis (CC; considering patients who provide baseline, post, and/or follow-up data) will be performed. ANCOVAs with treatment as the between-subject factor (MCT-OCD vs. care as usual control group), the baseline level of the respective outcome as the covariate, and the difference in the scores of the outcomes (t1 – (−t1) and t2 – (−t1), respectively) as the dependent variable will be conducted [91]. Differences between the groups at baseline (−t1) will be analysed by an independent samples *t*-test (for continuous variables) or a chi-square test (for categorical variables). For the intention-to-treat analyses, multiple imputation will be used for missing values. The number of patients that attained response and/or remission will be reported following the suggestions by Mataix-Cols et al. [21]. Additional regression analyses will be conducted in order to identify variables (severity of baseline OCD symptoms, baseline depression, number of sessions completed, and type of OCD symptoms [e.g., washing, checking], prior therapy experiences etc.) that contribute to the treatment effectiveness of the MCT-OCD.

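### Destroying the data of patients who withdraw consent after randomisation removes them from the intention-to-treat set that the plan defines

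*Protocol article*

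**What the plan says.** Three parts of the protocol article bear on this.

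- **Study design and ethical aspects:** when a participant withdraws consent to take part, "the reasons will be carefully documented and the collected data will be destroyed and deleted". No time limit is given, and randomised patients are not treated differently.
- **Randomization and assessor blindness:** allocation comes after the baseline assessment. The section then adds: "Withdrawal from the intervention or assessments will be possible at any time". No deletion is attached to that kind of withdrawal.
- **Statistical analyses:** the set is described as "An intention-to-treat analysis (considering patients who provide baseline data", and "For the intention-to-treat analyses, multiple imputation will be used for missing values". A complete-case analysis runs alongside.

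The Sample size section expects 15% dropout among 80 randomised patients. It does not say what share would be withdrawals of consent.

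**The concern.** Every randomised patient has baseline data at allocation and so belongs to the intention-to-treat set. If that patient later withdraws consent to take part, the ethics section orders those same data destroyed. Both provisions cannot be met for that patient, and the result is an exclusion after randomisation.

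Such exclusions matter most when they depend on arm and on how the patient is doing. Patients learn their arm by letter. Entry requires willingness to take part in the training, so controls are people who were prepared to attend it. Controls are offered the training after follow-up, which gives them a reason to stay; the intervention arm has no matching incentive. The Discussion accepts that expectancy effects cannot be eliminated with this control.

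The boundary is also loose. The document does not say whether a patient who stops both sessions and assessments has thereby withdrawn consent to take part. The same patient could be kept and imputed, or erased, on a classification made after the patient knows the arm.

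**Working it through.** **1. The provisions side by side.** The order of events is baseline, randomisation, t1 at 8 weeks, and t2 three months after t1.

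| What the patient does | Data already collected | Intention-to-treat set |
|---|---|---|
| Stops sessions | Kept | In; t1 observed or imputed |
| Stops assessments | Kept | In; missing values imputed |
| Withdraws consent before t1 | Destroyed | Out; nothing to impute from |
| Withdraws consent after t1 | Destroyed, including the observed primary outcome | Out |

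Only the last two rows conflict with the analysis section.

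**2. How many.** The plan gives no figure for consent withdrawals. Its only related figure is the 15% expected dropout: 0.15 × 80 = 12 patients, leaving 68. This is an upper bound under the plan's own expectation, because dropout also includes the first two rows.

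**3. How far an arm mean could move.** Let w be the share of an arm that is deleted, R the mean of those retained and D the mean of those deleted. The mean of the whole arm is (1 − w)R + wD, so deletion shifts it by R minus that, which is w(R − D). The inputs are assumptions, not figures from the document: w from 2.5% to 15% (1 to 6 of 40), and R − D from 0.5 to 1.0 SD.

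- Low end: 0.025 × 0.5 = 0.0125, about 0.01 SD.
- High end: 0.15 × 1.0 = 0.15 SD.

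If both arms lose patients, the contrast shifts by the difference between the two products. Equal losses with equal gaps cancel, and larger losses among controls can reverse the sign.

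**4. How much of that shift is due to the deletion rule.** Take an example in which intervention patients who withdraw before t1 gain nothing and the rest gain the planning effect of 0.80 SD.

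| Share withdrawing | Full-data effect, (1 − w) × 0.80 | Data deleted | Baseline kept, imputed from arm and baseline |
|---|---|---|---|
| 5% | 0.76 | 0.80 | 0.80 |
| 10% | 0.72 | 0.80 | 0.80 |
| 15% | 0.68 | 0.80 | 0.80 |

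The last two columns agree because an imputation model using only arm and baseline learns from the retained patients and gives the withdrawers their pattern. The gap of 0.04 to 0.12 SD comes from t1 scores that were never observed, and keeping baseline data would not close it. Deletion does harm of its own in two situations: when a t1 score already exists and is destroyed, and when other collected data would have helped to predict the missing score.

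**5. Power.** With a two-sided t-test at 0.05 (the plan does not state sidedness) and d = 0.80, power is 0.94 with 40 per arm, 0.92 if one arm falls to 34, and 0.90 if both do. The issue is bias rather than power. The same inputs at 80% power give N = 52, not the stated 70. That is a separate matter, and nothing here depends on it.

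**The case against.** The strongest case on the other side is that the rule is narrow. It is triggered by withdrawing consent to take part, and the document treats withdrawal from the intervention or the assessments separately, with no deletion. Ordinary dropouts stay in the intention-to-treat set and are imputed. The rule is part of an ethics-approved protocol and protects patients who want to leave. Consent withdrawals may be few, and for those who leave before t1, keeping baseline data recovers little under a simple imputation model.

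Most of this stands, and it rules out some stronger readings:

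- A reader might infer that every dropout is erased, so that intention-to-treat is impossible or becomes a completer analysis. The document does not support this, because patients with baseline data only remain in the set.
- A reader might take the 15% as the rate of erasure. It is overall dropout.
- A reader might fault the definition of the set by baseline data. Since randomisation follows baseline, that definition covers all randomised patients apart from those erased.
- A reader might object that neither analysis set is named as primary. An article commonly leaves that to the analysis plan.

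One thing is not answered. The deletion rule is stated, not omitted, and no analysis plan written later can restore destroyed data.

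**Conclusion.** The point holds in limited form. The deletion rule takes post-randomisation consent withdrawers out of the set that the analysis section defines, and they can be neither analysed nor imputed. The damage is proportional to their number, which the document does not give: between 0 and about 12 of 80 if the expected dropout is right.

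Under the assumed ranges an arm mean could shift by about 0.01 to 0.15 SD, but that is not an estimate of bias in this trial. The gap between withdrawers and the rest is unknown, losses may fall in both arms, and part of any shift would remain even if baseline data were kept. The clearest avoidable loss is a t1 Y-BOCS already in hand that is destroyed because the patient withdraws consent afterwards. The reason to act early is that deletion cannot be undone.

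**What to change.** For patients still to be enrolled, amend the withdrawal rule and the matching consent wording:

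1. Separate withdrawing from further participation from revoking the use of data.
2. On withdrawal from participation, keep the data already collected and analyse them in the allocated arm within the intention-to-treat set.
3. Erase data only on the patient's explicit request.

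For patients already enrolled, honour the existing promise.

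For all patients, report the number and timing of erasures by arm (before or after t1), and state that these patients are missing from the intention-to-treat set. The reasons for withdrawal are to be documented in any case, so this adds little work.

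The Trial status section says that recruitment was still open, that no data had been analysed and that changes would be recorded in an amendment, so the route exists. The cost is an ethics and consent amendment. It reaches only later enrolees, and explicit erasure requests will still lose data.

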### Sample size

To detect a medium to large effect size of *d* = 0.80, with an alpha level of α = 0.05 and a power of 0.80, G*Power [66] calculated a sample size of *N* = 70. As a dropout rate of 15% is expected, a sample of *N* = 80 patients with OCD will be recruited and randomized to the two groups (*n* = 40 MCT-OCD, *n* = 40 usual care control group). A diagnosis of OCD will be verified by the Mini International Neuropsychiatric Interview 5th Ed. (MINI 7.0.2) [67], which serves to elucidate further psychiatric diagnoses based on the *Diagnostic and Statistical Manual of Mental Disorders* (5th ed.) (*DSM-5*).

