The present approach unites the general features of the MCTs (e.g., open group concept, inclusion of “aha moments”) with the contents of a self-help manual for patients suffering from OCD called “myMCT” (for “my metacognitive training”) developed by Moritz, Jelinek, Hauschildt, and Naber [44]. The manual includes psycho-education about core elements of OCD (i.e., obsessions, compulsions, avoidance, and safety behaviors), offers patients support in identifying dysfunctional (meta-)cognitive biases as well as dysfunctional coping strategies, and provides new strategies. The myMCT has already shown to be superior to wait-list as well as active (psycho-education) control groups over a period of 4 weeks [44–46]. A recent meta-analysis showed an effect size of *SMD* = 0.40 [47]. Although significant effects were no longer present at the 6-month follow-up, change in (meta-)cognitive biases remained stable [45]. The nonsignificant effects at follow-up may potentially derive from the fact that the patients did not practice the exercises on a regular basis. Despite the generally positive subjective appraisal of the myMCT, 67 to 83% of patients mentioned that instead of using myMCT as a self-help treatment, they would like to use it in face-to-face psychotherapy [44, 45]. To meet this preference, we converted the myMCT to a group format that is comprised of four modules primarily targeting (meta-)cognitive biases and beliefs, and this was positively evaluated by patients in a pilot trial [48–50]. In the pilot trial patients with OCD participated in the MCT-OCD, which included four modules that were conducted over 4 weeks during their inpatient stay in a single-arm trial. Acceptability of the MCT-OCD was high; for example, 89.7% of the patients said they would recommend the MCT-OCD to others and thought the training was useful and understandable [48]. Furthermore, Miegel et al. [50] provided some evidence that the different modules indeed specifically improved targeted (meta-)cognitive biases and beliefs: for example, the subjective need to control thoughts was especially reduced after a module targeting control of thoughts. This indicates that the MCT-OCD modules specifically reduce the biases that are addressed in each module. Evaluation of the effectiveness of the MCT-OCD pilot study demonstrated that patients’ OC symptoms decreased with a large effect from baseline to post assessment (η^2^_partial_ = 0.50) [49]. However, the pilot study lacked a control group and included only patients currently undergoing a comprehensive inpatient treatment, limiting the conclusions.

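### The stated sample-size inputs (d = 0.80, alpha 0.05, power 0.80) give a total of 52, not 70, so the plan misstates its power and detectable effect, though conservatively for d = 0.80

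*Protocol article*

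**What the plan says.** The Sample size section of the protocol article makes two linked statements. The first sets the target, "To detect a medium to large effect size of *d* = 0.80", and gives the result: "with an alpha level of α = 0.05 and a power of 0.80, G*Power [66] calculated a sample size of *N* = 70". The second allows for losses: "As a dropout rate of 15% is expected, a sample of *N* = 80 patients with OCD will be recruited", split 40 and 40. Neither the test used in the calculation nor its sidedness is given.

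The Statistical analyses section plans an ANCOVA on the change score with the baseline value as covariate. It is to be run by intention to treat with multiple imputation, and on complete cases. The primary outcome is the reduction in Y-BOCS total score from baseline to post assessment. Nothing elsewhere in the article explains the figure of 70.

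**The concern.** The effect size, alpha, power and resulting N are printed together, and they do not agree. At least one of them is misreported, or the calculation run was not the one described. The article does not show which.

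This matters when the result is read. If d = 0.80 was the intended target, the trial has more power than it claims. If the intended target was nearer 0.68 (two-sided, 80% power), the printed effect is too large and the design has no reserve. A reader weighing a non-significant result needs to know which of these applies, and whether the test was planned one- or two-sided.

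The allowance for dropout does not return the stated requirement either, although that slip is small.

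**Working it through.** **Inputs.** From Sample size: d = 0.80, alpha 0.05, power 0.80, required N = 70, dropout 15%, recruited N = 80, equal arms. Sidedness is not stated, so both are tried.

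**Step 1: try to reproduce 70.** For n per arm, exact power comes from the noncentral t distribution with 2n − 2 degrees of freedom and noncentrality d × √(n/2).

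- Rough check by normal approximation, two-sided: n = 2 × (1.960 + 0.842)² / 0.80² = 24.5, so 25 per arm and N = 50.
- Exact, two-sided: n = 26 gives noncentrality 0.80 × √13 = 2.88 and power 0.807; n = 25 gives 0.791. So N = 52.
- Exact, one-sided: n = 21, so N = 42.
- ANCOVA F-test, f = d/2 = 0.40, one numerator degree of freedom: N = 52 with no covariate or one.
- Crediting the baseline covariate lowers N further: 48, 40 or 28 for assumed baseline-post correlations of 0.3, 0.5 or 0.7.
- Mann-Whitney, with relative efficiency 0.955 or 0.864: N = 56 or 62.

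None of these gives 70. The excess over 52 is 18 patients, or 18/52 = 35%, which is too large for rounding.

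**Step 2: find which changes give about 70.**

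| Changed input | Total N |
|---|---|
| d = 0.68, two-sided, power 0.80 | 70 |
| d = 0.80, one-sided, power 0.95 | 70 |
| d = 0.80, two-sided alpha 0.025, power 0.85 | 70 |
| d = 0.80, two-sided, power 0.90 | 68 |
| d = 0.60, one-sided, power 0.80 | 72 |

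**Step 3: dropout.** 80 × 0.85 = 68. To keep 70 after 15% loss needs 70 / 0.85 = 82.4, that is 83, or 84 with equal arms. Recruiting 80 leaves 70 only if loss is 1 − 70/80 = 12.5%. Multiplying instead of dividing gives 70 × 1.15 = 80.5, which may be the source of 80.

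**Step 4: what the design delivers** (two-sided, unadjusted t-test).

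| Analysed | Power at d = 0.80 | Effect detectable with 80% power |
|---|---|---|
| 68 (34 per arm) | 0.902 | 0.69 |
| 70 (35 per arm) | 0.910 | 0.68 |
| 80 (40 per arm) | 0.942 | 0.63 |

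With the planned ANCOVA the detectable effect shrinks by √(1 − r²), where r is the baseline-post correlation. The article gives no value for r. With 68 analysed:

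| Assumed r | √(1 − r²) | Detectable effect (0.69 × factor) | Power at d = 0.40 |
|---|---|---|---|
| 0 (unadjusted) | 1.000 | 0.69 | 0.37 |
| 0.3 | 0.954 | 0.66 | 0.40 |
| 0.5 | 0.866 | 0.60 | 0.47 |
| 0.7 | 0.714 | 0.49 | 0.62 |

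**The case against.** The strongest defence is that the error is on the safe side. The stated inputs need 52 analysed, or 52 / 0.85 = 61.2, so 62 recruited, and 80 are planned. That stands: for d = 0.80 the trial has more power than it states.

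The dropout slip is also minor. It costs two completers and takes power at d = 0.80 from 0.910 to 0.902, under one percentage point. If the true requirement is 52, it has no effect at all.

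A fuller protocol or analysis plan could name the test and sidedness. It could not make the printed inputs yield 70, so this is a contradiction within the article and not a detail left to another document.

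Two stronger readings are tempting and are not supported.

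- **That the trial is underpowered.** A reader might infer this because the Background reports for the related self-help manual that "A recent meta-analysis showed an effect size of *SMD* = 0.40", and effects of 0.34 and 0.38 in size for the parent training in psychosis. Those are different formats or a different disorder. The Background also gives g = 0.97 for group therapy in OCD against wait-list controls. Whether 0.80 is optimistic is a judgement about assumptions, separate from the arithmetic. A single power figure of 0.37 at d = 0.40 would also ignore the planned baseline adjustment.
- **That the source of the error can be identified.** For instance, 68 / 0.85 is exactly 80, which would fit d = 0.80 two-sided at 90% power. This is inference only, as the article does not say so.

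**Conclusion.** The sample-size statement is wrong as written. The printed inputs give 52 two-sided or 42 one-sided, against 70 stated, and no standard test tried with those inputs gives 70. The dropout step is a minor second error (68 left, not 70).

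The consequence is a misstated power and detectable effect. It is not a shortage of patients for the stated target: with 68 analysed, two-sided power at d = 0.80 is about 0.90.

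The figures for N rest only on the printed inputs and equal arms. Those for what the design delivers assume a two-sided test and information equal to that of 68 completers. The ANCOVA figures also assume a baseline-post correlation, which the article does not give, and are therefore shown as a range.

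**What to change.** Keep N = 80. In the Sample size section:

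1. Check the G*Power record and state the test, the sidedness and the inputs that produced 70. Correct whichever printed input is wrong. The replacement should come from that record and not be back-calculated to fit.
2. Correct the dropout sentence: 80 recruited with 15% loss leaves 68.
3. Restate what the design delivers. If the test is two-sided, suitable wording is: with 68 analysed (34 per arm), an unadjusted t-test at alpha 0.05 has about 90% power for d = 0.80 and 80% power for d = 0.69; with the planned ANCOVA the detectable effect is about 0.66, 0.60 or 0.49 for assumed baseline-post correlations of 0.3, 0.5 or 0.7.
4. If power at d = 0.40 is quoted, give it as a range, from about 0.37 unadjusted to 0.62 at a correlation of 0.7.
5. Record the correction as an amendment, as the Trial status section provides, since enrolment began in February 2018.

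The cost is wording and one look at the original calculation. Recruitment, allocation and the planned analysis do not change.

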### Recruitment

Participants will be recruited via the anxiety outpatient clinic of the Clinic for Psychiatry and Psychotherapy of the University Medical Center Hamburg-Eppendorf (Germany), local therapists, Google AdWords, the German society for OCD (DGZ), posters, and brochures. Individuals who have already participated in prior studies of our working group and have given their written informed consent for future contact will also be contacted. Patients who already participated the MCT-OCD pilot version were not contacted again. Patients who read the myMCT were not excluded but this was carefully documented.

### In- and exclusion criteria

In order to be able to generalize the results to a broad population of OCD patients, the eligibility criteria for the recruitment of the sample have been chosen carefully. The following criteria have to be fulfilled to be included in the proposed study: Participants need to (a) be between 18 and 70 years of age; (b) have a diagnosis of OCD according to the MINI; (c) demonstrate the willingness to participate in the MCT-OCD training and provide informed consent; (d) be available to attend the weekly sessions, and (e) be suitable for group therapy. Nationality will be assessed during a telephone interview, and if the potential participant reports a non-German nationality, the interviewer will explore whether they have sufficient language comprehension. The patients’ suitability for participating in a group setting will be assessed during the screening verifying the social skills of the patients during the interview (e.g., whether patients can attend group rules, such as not to insult others). All participants receiving any kind of outpatient psychotherapy (e.g., CBT, CT, psychodynamic) and/or pharmacological treatment (e.g., SSRI, antidepressants) will be able to continue this treatment as usual. All treatments will be documented thoroughly throughout the study. Additional to the kind of treatment, the number of past treatments as well as the number of sessions of the current treatment will be assessed. The exclusion criteria are (a) current or lifetime psychotic symptoms (e.g., mania), (b) a severe neurological disease, (c) current substance dependence, and (d) current inpatient treatment.

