Besides showing promising in-session as well as between-session effects, the MCT-OCD in its pilot version has also been shown to be highly accepted by patients with OCD [48], to have module-specific positive effects [50], and to result in a reduction of OC symptoms with large effect sizes [49]. As OCD patients often do not receive the most effective treatment for OCD (CBT with ERP), the MCT-OCD aims to provide a treatment option that is low threshold and highly accepted by patients. If proven effective against care as usual, it may help reduce the burden of OCD, as the MCT-OCD is highly standardized and easy to administer and can therefore be integrated quickly and economically into everyday clinical practice. As part of a larger stepped-care approach, MCT-OCD could, for example, be used as a sole intervention for mild cases or to bridge waiting times and ease the start of treatment with ERP.

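### The primary contrast estimates MCT-OCD added to mixed usual care: it does not itself test sole or waiting-time use, and the ANCOVA leaves out concurrent treatment recorded at baseline

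*Protocol article*

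**What the plan says.** - **Who may enter.** Under In- and exclusion criteria: "All participants receiving any kind of outpatient psychotherapy (e.g., CBT, CT, psychodynamic) and/or pharmacological treatment (e.g., SSRI, antidepressants) will be able to continue this treatment". No criterion on stability or stage of that treatment is listed. The same section says the criteria were chosen so that results generalize widely across people with OCD.
- **What care as usual means.** The Aim of the present study allows patients both to continue existing treatment and to begin a new one.
- **What is recorded.** All treatments are documented during the study, including the kind of treatment, the number of past treatments and the number of sessions of the current one. Dates of starting or changing medication are not mentioned.
- **How it is analysed.** Statistical analyses fixes "ANCOVAs with treatment as the between-subject factor (MCT-OCD vs. care as usual control group), the baseline level of the respective outcome as the covariate". Further regressions may examine prior therapy among other variables; concurrent therapy is not named, though the list is open-ended.
- **What use is suggested.** The Discussion says that, if effective against care as usual, MCT-OCD could, within stepped care, "be used as a sole intervention for mild cases or to bridge waiting times and ease the start of treatment with ERP". Its limitations paragraph names four limitations, and concurrent treatment is not among them.

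**The concern.** The Abstract and Background motivate the trial by patients who do not get CBT with ERP, decline it or wait months for psychotherapy. The suggested uses follow that motivation. The sample is wider: someone in active CBT or on an SSRI can enter, and for that person MCT-OCD is an add-on. One pooled contrast averages add-on and stand-alone effects and does not separate them.

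The article applies this standard elsewhere. It says the pilot's conclusions were limited because all its patients were in comprehensive inpatient treatment, and it faults another study for not controlling for pharmacotherapy.

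Two things are at stake. A positive result could be read as evidence for stand-alone use that the main estimate does not supply. And a baseline variable likely to predict 8-week change is recorded but left out of the model, which gives up some precision with 40 per arm.

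**Working it through.** **The plan's own figure.** The Sample size section gives a "medium to large effect size of *d* = 0.80", "with an alpha level of α = 0.05 and a power of 0.80", and reports that "G*Power [66] calculated a sample size of *N* = 70". Two-sided, these inputs give 25.5, so 26 per arm and N = 52; N = 70 has power 0.91. The stated figure does not reproduce. That is a separate matter and neither supports nor weakens this point. What is needed here is the number of completers at the stated 15% dropout: 80 × 0.85 = 68, with power 0.90 at d = 0.80 for the pooled contrast.

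**Step 1: what the pooled effect says about untreated patients.** With equal SDs, pooled d = s × d(untreated) + (1 − s) × d(treated), where s is the untreated share. The documents do not give s, so s = 0.40 is an assumption. For a pooled d of 0.80:

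- d(treated) = 0.4: (0.80 − 0.60 × 0.4)/0.40 = 1.4
- d(treated) = 0.8: 0.8
- d(treated) = 1.2: (0.80 − 0.60 × 1.2)/0.40 = 0.2

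The same main result is compatible with a large or a small stand-alone effect.

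**Step 2: how much a subgroup estimate could settle.** Two-sided t-test, d = 0.80, 68 completers split equally:

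| Untreated share (assumed) | Per arm | Power |
|---|---|---|
| 20% | 6.8 | 0.27 |
| 40% | 13.6 | 0.52 |
| 50% | 17 | 0.62 |
| 75% | 25.5 | 0.80 |

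Unless about three quarters are untreated, the subgroup estimate will be imprecise.

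**Step 3: chance imbalance.** Assume a treated share p of 0.3 to 0.5, a treatment effect on change δ of 3 to 5 Y-BOCS points, and an outcome SD of 6.

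- SD of the difference in treated share = √(2p(1 − p)/40) = 0.102 (p = 0.3) or 0.112 (p = 0.5).
- 95% range: × 1.96 = ±20 to ±22 percentage points.
- Shift in the arm difference at the edge of that range: 0.20 × 3 = 0.6 to 0.22 × 5 = 1.1 points. A typical (1 SD) shift is 0.102 × 3 = 0.31 to 0.112 × 5 = 0.56.
- Standard error of the arm difference = 6 × √(2/40) = 1.34 points.

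Even the edge lies within one standard error, and the confidence interval already allows for it.

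**Step 4: what adjustment gains.**

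- Variance share = p(1 − p)δ²/36 = 0.21 × 9/36 = 0.05 to 0.25 × 25/36 = 0.17.
- Shortening of the standard error = 1 − √(1 − 0.05) ≈ 3% to 1 − √(1 − 0.17) ≈ 9%.
- Cost at 68 completers: residual degrees of freedom fall from 68 − 3 = 65 to 63 with two added covariates.

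**The case against.** The strongest reply is that the aim, eligibility, comparator and analysis all fit one question: MCT-OCD offered on top of usual care to a wide outpatient population. Pooling is what that question calls for, and randomization keeps the comparison valid. The Background is motivation and does not define the target population. The Discussion is conditional and gives its uses as examples. Covariates and subgroups may also be extended in an analysis plan that is not shown. Nearly all of this stands.

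A reader might go further and infer that the trial cannot inform sole or waiting-time use, that it concludes for patients without CBT with ERP, or that imbalance in concurrent treatment biases the result. The documents support none of these. Untreated and waiting patients are eligible and their treatment is recorded, so exploratory evidence is possible. The suggested use is hedged. Chance imbalance affects precision and adds no bias. Entry at any stage of treatment is inferred from the absence of a criterion; the article does not state it. The absence of a planned subgroup estimate from a condensed article is no fault in itself.

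The reply leaves two things standing. Sole or bridging use goes beyond what the primary contrast estimates, with no matching limitation. And the article does fix the ANCOVA covariate, omitting a recorded baseline variable that could be used at almost no cost.

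Subgroups also need careful naming. Patients without psychotherapy may still take medication, so that group alone does not represent sole treatment. Nor is it the same as patients without CBT with ERP, since some psychotherapy does not include ERP.

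**Conclusion.** The point holds as a minor one. The main result will be an effect of MCT-OCD added to mixed usual care, valid for the broad population declared, and it does not by itself show an effect as the only treatment or during a wait. With an assumed 40% untreated, a pooled d of 0.80 fits untreated effects from 0.2 to 1.4 as the treated effect runs from 1.2 down to 0.4. Adjusting for concurrent treatment at baseline would shorten the standard error by about 3% to 9%. That range rests on three assumptions not found in the documents: 30% to 50% treated, a 3 to 5 point effect on change, and an SD of 6. It would be smaller if stable long-term treatment predicts little change over 8 weeks. Reading this as a fault in the eligibility criteria or in the validity of the comparison would be too strong.

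**What to change.** - **Statistical analyses.** Add current psychotherapy (yes/no) and current psychotropic medication (yes/no), both as recorded at baseline, as prespecified ANCOVA covariates. Use recent start or change of medication only if those dates are actually collected. Keep to baseline status: treatment begun after randomization belongs to care as usual and may depend on allocation.
- **Exploratory estimates.** Report the effect with its confidence interval in patients with neither psychotherapy nor medication at baseline, and in those without psychotherapy, labelled exploratory and probably imprecise.
- **Discussion.** Describe the main result as MCT-OCD added to care as usual, say that sole or bridging use is not tested directly by the primary contrast, and list concurrent treatment among the limitations.

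The cost is one or two degrees of freedom and a few sentences. Recruitment does not change, and the two yes/no covariates should need no new data, because the kind of treatment is already documented.
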